### 6.1.5 **Brief summary of non-clinical findings:**

- When *Lactobacillus* expressing CXCL12 is applied topically, the expression of CXCL12 is significant for approximately one hour. The efficacy has been investigated in open dry uncovered wounds in mice and in wounds covered by a film dressing resulting in a moist enclosed wound environment in minipigs. There is no colonization of the wounds by the *lactobacilli* and in uncovered wounds, close to all *lactobacilli* die within one hour. When the wounds are enclosed with a film dressing, some *lactobacilli* can be found on the skin immediate to the wound after 2 to 3 days.
- Administration of *Lactobacillus* expressing CXCL12 to induced wounds in mice daily until healing (ca 8 days) resulted in an acceleration of wound closure as compared to no treatment, treatment with native *Lactobacillus* or recombinant CXCL12.
- Administration of *Lactobacillus* expressing CXCL12 to induced wounds on 15 occasions over 4 weeks in minipigs was associated with an acceleration of wound closure and reduction of scar size.
- *Ex vivo* treatment of human dermal wounds with *Lactobacillus* expressing human CXCL12 for up to 14 days showed increased epithelialization compared to no treatment.
- CXCL12 promotes wound healing by inducing proliferation and phenotype shift of local macrophages in the dermis close to the wound area, resulting in increased expression of TGF- $\beta$ . In addition, the reduced local pH as a result of lactic acid produced by the *lactobacilli* inhibits degradation of the delivered CXCL12. Thus, the system with a continuous delivery of CXCL12 in low doses for a short time close to the wound surface and inhibition of inactivation results in a local increase of CXCL12 binding to its receptor CXCR4 on the target cells that induce the phenotype shift.
- The MOA was outlined in multiple studies investigating effects of recombinant- and *Lactobacillus*-derived CXCL12 and included investigations where the target immune cells were blocked. Treatment effects were also studied in mouse models of ischemia and hyperglycemia.

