### 6.2 Study rationale

The present study aims to evaluate safety, tolerability, exposure and preliminary efficacy following application of activated ILP100-DP on experimentally induced, full thickness wounds in healthy volunteers.

A FIH study in healthy subjects with multiple induced wounds is proposed as the first study on activated ILP100-DP rather than a Phase I/II study in patients with DFUs based on the novelty of the API and the heterogeneity among 1) patients with DFUs and 2) the microenvironment in the different DFUs that could also be different in different locations.

In addition, with the proposed design, safety can be evaluated by early biopsies of the wounds determining the exact amount of the bacterial-delivered hCXCL12 to the immediate wound tissue.

The study is intended to provide important information to support the design of further studies in patients.

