| To determine the effect of activated ILP100-DP on CXCL12 levels in the wound (biopsy; single ascending dose [SAD] part only) and in blood (SAD and MAD part) | Relationship between dose of activated ILP100-DP and levels of CXCL12 in biopsies (SAD) and plasma (SAD+MAD)                                            | SAD+ MAD |            | Biopsies for analysis of CXCL12 in the wound (Section 11.8.2)

Blood sampling for analysis of CXCL12 in plasma (ELISA; Section 11.8.1) |

| Objective                                                                                         | Endpoint                                                                              | Part     | Evaluator                                                                          | Assessment(s)                                                |
|---------------------------------------------------------------------------------------------------|---------------------------------------------------------------------------------------|----------|------------------------------------------------------------------------------------|--------------------------------------------------------------|
| To compare histopathology from wound biopsies after treatment with activated ILP100-DP or placebo | Overall histopathology evaluation (normal/abnormal wound healing process)             | SAD      | Evaluated by histopathologist                                                      | Biopsies for histopathology (Section 11.8.2)                 |
|                                                                                                   | Immune cell infiltration close to the wound area and CXCL12 (relative amounts)        | SAD      | [figure not shown] | Biopsies for immunohistochemistry (Section 11.8.2)           |
| To assess the time-course of wound healing                                                        | Relationship between dose of activated ILP100-DP and the time course of wound healing | SAD+ MAD | Investigator (direct observation)

Independent evaluators (photography)      | Wound healing definition (Section 11.8.3)                    |

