15. CXCL12 blood sampling at 9:00±2 hours. On Day 2: 24h±2 hours post dose but no later than 11:00. On Day 3 and 14, also plating of blood samples prior to centrifugation for blood culturing, see Section 11.8.1 and Section 11.8.1.2.
16. 48 hours after IMP administration (one biopsy from a CXCL12 treated wound and one from a placebo treated wound)
17. Wound healing assessed by the Investigator (direct observation) and by 3 to 5 independent evaluators using photographs.
18. Wound area assessed by 3 to 5 independent evaluators using photographs and the Image J software (National Institutes of health [NIH]) or equivalent.
19. Baseline wound area measurements based on photos taken after wound punching prior to IMP application.
20. Scar tissue formation assessed by the Investigator (direct observation) and by 3 to 5 independent experts using photographs at Visit 6. Scar tissue formation during the long-term follow-up assessed by the Investigator only. Normal/abnormal and Vancouver scar scale. One assessment per wound.
21. Dressing if indicated.
22. From administration of IMP.
23. Collection of AEs including, but not limited to, mortality, development of any new/recurrent cancer, development of infection, immunogenicity related reactions.
24. For definitions of prior and concomitant medications, see Section 11.3.6.

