### 8.1.2 *Multiple Ascending Dose (MAD)*

Part II of the study will explore multiple ascending dosing of *L. reuteri* expressing CXCL12 (activated ILP100-DP) in 3 sequential cohorts, each of 8 subjects. For each subject in a cohort, activated ILP100-DP, placebo and saline (NaCl) will be randomized to in total 8 wounds, 4 on the right arm and 4 on the left, in a 4:2:2 ratio (i.e. 4 wounds will be treated with activated ILP100-DP, 2 wounds will be treated with placebo and 2 wounds will be treated with saline as randomized). Activated ILP100-DP will be randomized to one of the arms and placebo and saline to the other arm. The IMPs will be administered on Day 1, Day 2 and Day 3 and then 3 times a week over the course of 3 weeks (in total 10 doses).

The proposed dose levels are  $5 \times 10^5$ ,  $5 \times 10^7$  and  $1 \times 10^9$  CFU/cm^2 wound area. The rationale for the starting dose and the planned dose escalation is detailed in Section 8.3. The doses, dose escalations and the dosing schedule may be adjusted based on emerging knowledge of safety and tolerability data observed in the SAD part of the study.

Subjects will come for 13 visits to the research clinic for screening, treatment and initial follow-up (Visit 1 to Visit 13), see Table 8.1-2 for details. After Visit 13, a 5-year long-term follow-up period (Visit 14 to 21) will be initiated as detailed below.

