14. CXCL12 blood sampling prior to wound punching at 9:00±2 hours, 1 hour post the last wound punch (within 5 minutes of start of IMP application, which should start 1 hour (+/-10% post the last wound punch) and 1 hour (±10%) after the last IMP application.
15. Pre-treatment. The pre-treatment sample should be taken at 9:00±2 hours.
16. Pre-treatment on Day 5, 8, 15 and 19. The pre-treatment samples should be taken at 9:00±2 hours.
17. On Day 3, 5, 8, 15 and 21, also plating of blood samples prior to centrifugation for culturing, see Section 11.8.1 and Section 11.8.1.2.
18. The CXCL12 blood sample should be taken at 9:00±2 hours.
19. Pre-dose Day 1 and pre-dose on Day 19, see Section 11.8.1.
20. Wound healing assessed by the Investigator (direct observation) and by 3 to 5 independent experts using photographs. No assessment by independent experts on Day 17.
21. Wound area assessed by 3 to 5 independent experts using photographs and the Image J software (NIH) or equivalent.
22. Baseline wound area measurements based on photos taken after wound punching prior to IMP application.
23. Scar tissue formation assessed by the Investigator (direct observation) and by 3 to 5 independent experts using photographs Visit 9 to Visit 12. Scar tissue formation during the long-term follow-up assessed by the Investigator only. Normal/abnormal and Vancouver scar scale. One assessment per wound.
24. Day 5, Visit 5.
25. Day 15, Visit 9.
26. At any time between Day 15 and Day 21.
27. Just prior to treatment on Day 2, Day 8 and Day 15.
28. Dressing if indicated.
29. Dressing collection on Day 2 (applied Day 1), Day 3 (applied Day 2).
30. From administration of IMP.
31. Collection of AEs including, but not limited to, mortality, development of any new/recurrent cancer, development of infection, immunogenicity related reaction.
32. For definitions of prior and concomitant medications, see Section 11.3.6.

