## **11.8 Assessments related to secondary endpoints**

### **11.8.1 Blood sampling for analysis of systemic exposure of CXCL12 in plasma and *L. reuteri* in blood**

Venous blood samples (approximately 5 mL) for the determination of plasma concentrations of CXCL12 (Section 11.8.1.1), for blood culturing (Section 11.8.1.2) for analysis of *L. reuteri* in blood, for future exploratory analyses (11.8.1.1) and for future PBMC analysis (Section 11.8.1.3), will be collected through venipuncture or an indwelling venous catheter at pre-specified visits (see Table 8.1-1 and Table 8.1-2). The blood samples will be collected in pre-labelled EDTA-K2 tubes.

The date and time of collection of each sample will be recorded in the eCRF.

On Day 3 and 14 of the SAD part (Visit 4 and Visit 5), and on Day 3, 5, 8, 15 and 21 of the MAD part (Visits 4, 5, 6, 9 and 12), 200 µL of the venous blood sample should be plated for blood culturing prior to centrifugation for plasma collection as described in Section 11.8.1.2.

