### 17.6 *Analysis of secondary endpoints*

#### 17.6.1 *CXCL12 levels in blood and in the wound*

Relationship between dose of activated ILP100-DP and levels of CXCL12 in wound biopsies and blood (SAD part only) will be presented by correlation analysis.

Relationship between dose of activated ILP100-DP and the time course of complete wound healing/closure (SAD and MAD parts) will be presented by correlation analysis.

Actual CXCL12 levels in the wound (SAD only) and in the blood (SAD and MAD) together with absolute and percent change will be presented using summary statistics.

*L. reuteri* R2LC colonies following blood culture will be presented using summary statistics by treatment, visit and cohort.

The colonies will be presented both as actual values and by logarithm scale (10 log).

All data will be listed by cohort, treatment (biopsy data) and subject.

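### No blood culture is timed to the first hours after a dose, although a 1-hour tube is already drawn, and Section 17.6.1 leaves MAD plasma out of the dose–CXCL12 correlation that the endpoint requires

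*Protocol*

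**What the plan says.** **Endpoints.** Section 7.2.1 of the Protocol lists, as secondary endpoints in both parts, the levels of CXCL12 and of *L. reuteri* R2LC in blood after dosing. A note in the same table says that the blood culture serves two separate objectives, exposure and colonization. The dose–exposure endpoint is the relationship between dose and "levels of CXCL12 in biopsies (SAD) and plasma (SAD+MAD").

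**Culture times.** For SAD, Table 8.1-1, footnote 15: "On Day 3 and 14, also plating of blood samples prior to centrifugation for blood culturing". For MAD, Table 8.1-2, footnote 17: "On Day 3, 5, 8, 15 and 21, also plating of blood samples prior to centrifugation for culturing". Footnotes 15 and 16 of the MAD table make the draws on Days 3, 5, 8 and 15 pre-treatment. Day 21 comes after the last dose, on Day 19.

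**A tube drawn soon after dosing.** Footnote 14 of both tables schedules a Day 1 blood sample for CXCL12 at 1 h (±10%) after the last application. No plating of that sample is scheduled.

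**What is known of timing.** Section 6.1.5 says that after topical application "the expression of CXCL12 is significant for approximately one hour". It reports near-complete bacterial death within an hour only for uncovered wounds. Under film, some lactobacilli were found on adjacent skin after 2 to 3 days.

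**Analysis.** Section 17.6.1 says that the relationship between dose and "levels of CXCL12 in wound biopsies and blood (SAD part only) will be presented by correlation analysis". The same section summarises blood CXCL12 descriptively for both parts.

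**Visit label.** Section 11.8.1 places the SAD plating "On Day 3 and 14 of the SAD part (Visit 4 and Visit 5"). In Table 8.1-1, Visit 5 is Day 7 and Visit 6 is Day 14.

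**The concern.** The culture has two jobs, and the schedule serves only one of them well. Samples taken a day or more after a dose can show whether the organism persists or propagates. They say little about whether viable bacteria enter the blood in the hours after application to a fresh full-thickness wound, which is what an after-dosing exposure endpoint should cover first.

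The non-clinical programme did sample early. Section 6.1.6 describes mouse blood taken three hours after wounding and treatment, and first-day minipig blood that included a draw 1 h after treatment. The human cultures do not repeat those times, so negative cultures here could not confirm the animal finding for the early period.

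The second issue is a contradiction in the text. An endpoint defined for SAD and MAD plasma has a planned correlation restricted to SAD. If followed literally, the part with repeated dosing and four active wounds per subject instead of two contributes nothing to the stated dose–plasma relationship.

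**Working it through.** **Inputs.** MAD doses on Days 1, 2 and 3 (Section 8.1.2) and on Days 5, 8, 10, 12, 15, 17 and 19 (Table 8.1-2). MAD cultures on Days 3, 5, 8, 15 and 21. SAD dose on Day 1, cultures on Days 3 and 14. MAD pre-treatment and Day 21 samples at 9:00 ± 2 h. Dosing in the morning (Section 10.6).

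**The plan's own figure.** 3 + 7 = 10 doses, the last on Day 19. This agrees with Section 8.1.2: "3 times a week over the course of 3 weeks (in total 10 doses").

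**Time since the previous dose.** Interval = (culture day − latest earlier dosing day) × 24 h.

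| Part | Culture day | Previous dose | Nominal interval |
|---|---|---|---|
| SAD | 3 | Day 1 | 48 h |
| SAD | 14 | Day 1 | 312 h (13 days) |
| MAD | 3 | Day 2 | 24 h |
| MAD | 5 | Day 3 | 48 h |
| MAD | 8 | Day 5 | 72 h |
| MAD | 15 | Day 12 | 72 h |
| MAD | 21 | Day 19 | 48 h |

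The shortest nominal interval is 24 h. To allow for clock time on MAD Day 3, take morning to mean 7:00 to 12:00 (an assumption) and the sample at 7:00 to 11:00:

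- shortest: 24 + 7 − 12 = 19 h
- longest: 24 + 11 − 7 = 28 h

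Visit-day windows are not applied in the table. MAD visits from Day 12 to Day 21 carry ±1 day, which can shorten or lengthen the last two intervals, and SAD Day 14 also carries ±1 day. No footnote ties a culture to a time shortly after dosing.

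**Effect of plating the existing tube.** 60 min × 0.9 = 54 min and 60 min × 1.1 = 66 min. The shortest interval would fall from about 48 h (SAD) and about 24 h (MAD) to 54–66 minutes. Plating uses 200 µL of a sample of approximately 5 mL (Sections 11.8.1 and 11.8.1.2): 0.2 / 5 = 4% of the tube.

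**The correlation.** SAD: 3 cohorts × 4 = 12 subjects. MAD: 3 × 8 = 24. Total 36. Restricting the blood correlation to SAD omits 24 of 36 planned subjects, or two thirds. Three statements on the scope of blood CXCL12 stand side by side:

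- Section 7.2.1, endpoint: plasma in SAD and MAD.
- Section 17.6.1, correlation: biopsies and blood, SAD only.
- Section 17.6.1, descriptive summary: wound in SAD only, blood in SAD and MAD.

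The correlation sentence is the one out of line.

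**The visit label.** Section 11.8.1 pairs SAD Days 3 and 14 with Visits 4 and 5. Table 8.1-1 pairs Day 3 with Visit 4, Day 7 with Visit 5 and Day 14 with Visit 6. The MAD visit numbers in the same sentence of Section 11.8.1 do agree with Table 8.1-2.

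**The case against.** Several stronger readings are tempting, and the Protocol does not support them.

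- **That bacteria survive only about an hour, so the later cultures are uninformative.** The one-hour figure in Section 6.1.5 is for expression. Rapid death is reported only for uncovered wounds. This trial uses film, in MAD around the clock for the first two days, and under film some bacteria were found on adjacent skin at 2 to 3 days. The SAD 48 h and early MAD cultures fall in or near that period and remain useful for propagation.
- **That no culture falls within 24 h of a dose.** MAD Day 3 is nominally at 24 h and can fall inside it. What stands is that none is aimed at the first hours.
- **That the exposure objective goes unanswered.** Plasma CXCL12 is drawn at 1 h on Day 1 in both parts, SAD biopsies are taken at about 48 h, and MAD plasma is summarised with absolute and percent change. The objective is partly answered.
- **That the small plated volume shows the size of the timing problem.** The 200 µL volume limits sensitivity at every time point, and would do so equally at 1 h.

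It is also fair to say that the SAD-only wording in Section 17.6.1 may be a misplaced qualifier, since Section 7.2 attaches it to the biopsy, and that Table 8.1-1 makes the intended visit fairly clear. Both are then wording corrections, but the text as it stands still conflicts. Finally, nothing says that negative cultures would be reported as absence of systemic exposure. Section 17.6.1 presents culture results by visit, so the sampling times stay visible.

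**Conclusion.** The point holds in limited form. All seven scheduled culture times are nominally 24 h or more after the previous dose, and none targets the first hours, so early bacteraemia is untested even though the culture is assigned an exposure role and a suitable tube is drawn on Day 1 in both parts. This rests on the nominal schedule, with the clock range for MAD Day 3 (19 to 28 h) depending on what morning dosing means. It is not a claim that the existing cultures are worthless.

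The conflict between Sections 7.2.1 and 17.6.1 needs no assumption. It removes 24 of 36 planned subjects from the dose–blood CXCL12 correlation, though not from the descriptive summaries. The visit mismatch for SAD Day 14 is minor but could misdirect one plating.

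**What to change.** 1. **Add one plating.** In footnotes 14 and 15 of Table 8.1-1, footnotes 14 and 17 of Table 8.1-2, and Section 11.8.1, add plating of 200 µL of the Day 1 sample taken 1 h after the last application, in both parts. Keep all scheduled cultures: dropping SAD Day 14 would remove the only late SAD blood culture for colonization. Leave the MAD pre-treatment draws where they are, since moving one would break that series. Cost: one additional culture per subject, with no extra venipuncture.
2. **Align the analysis with the endpoint.** In Section 17.6.1, attach the SAD-only restriction to wound biopsies alone, so that MAD plasma enters the dose–CXCL12 correlation. Cost: a wording change, using data already collected.
3. **Reconcile the visit number.** Bring Section 11.8.1 and Table 8.1-1 into agreement on the visit for SAD Day 14. Cost: a wording change.

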be checked as detailed in Table 8.1-2. There is immediate access to equipment, qualified staff and an ICU in case of an acute emergency. Up to 4 subjects will be dosed on the same day.

The wounds will be photographed in a standardized setting according to instructions specified in a separate manual, and briefly summarized in Section 11.5, before treatment on Day 1, pre-treatment at the subsequent dosing visits, and at all follow-up visits to the research clinic. Selected members of the clinical staff will receive photography training prior to handling of the camera equipment. In addition, wounds will be analyzed using a 3D camera as outlined in Section 11.9.1.

Following the first dose on Day 1, subjects will come for 10 additional visits between Day 2 and Day 21 (Visits 3 to 12). The last dose will be given on Day 19 (Visit 11). Safety will be assessed by vital signs, safety laboratory parameters, local tolerability, AEs, use of concomitant medications and CXCL12 ADA analysis at visits outlined in Table 8.1-2.

The wounds must not at any visit be cleaned (unless necessary for safety reasons, e.g. due to an infection). The area surrounding the wounds should then be carefully cleaned with water if necessary. At visits when swabbing is performed, the area around the wound should be cleaned after swabbing if necessary. Before the subject leaves the research clinic, the wound should be dressed until healed.

Blood sampling for analysis of CXCL12 and *L. reuteri* systemic levels and a swab of the area surrounding the wounds and feces sampling for analysis of any presence of *L. reuteri* R2LC colonies containing the pSIP411 plasmid will be performed at time points and visits specified in Table 8.1-2.

For exploratory purposes, microcirculation assessments will be performed and dressings will be collected at time points outlined in Table 8.1-2.

An end-of-treatment phase visit (Visit 13) will take place on Day 32 ( $\pm 1$  day) or after early withdrawal.

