| Assessment / Day                               | Day -28 to -1   | Day 1                     | Day 2                                                         | Day 3           | Day 5, 8, 10, 12, 15, 17, 19
±1 day on Days 12 to 19 | Day 21
± 1 day | Day 32
± 1 day                   | 6 weeks
± 3 days                           | 3 months
± 1 week | 6 months
± 1 week | 12 months
± 1 week | Once yearly
± 2 weeks | 5 years
± 1 month |
| Feces sample for analysis of L. reuteri |                 | X             |                                                               |                 |                                                         | X    |                                     | X                                             |                      |                      | X                     | X                        | X                    |
| Microcirculation                               |                 |                           | X                                                |                 | X                                          |                   |                                     |                                               |                      |                      |                       |                          |                      |
| Dressing                                       |                 | X                         | X                                                             | X               | X                                                       | X    |                                     |                                               |                      |                      |                       |                          |                      |
| Microbe analysis (dressing collection)         |                 |                           | X                                                | X  |                                                         |                   |                                     |                                               |                      |                      |                       |                          |                      |

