| Baseline symptoms                              | X               |                           |                                                               |                 |                                                         |                   |                                     |                                               |                      |                      |                       |                          |                      |
| AEs                                            |                 | X            | X                                                             | X               | X                                                       | X                 | X                                   | X                                | X       | X       | X        | X           | X       |
| Prior and concomitant medication  | X               | X                         | X                                                             | X               | X                                                       | X                 | X                                   | X                                             | X                    | X                    | X                     | X                        | X                    |

1. Or after early withdrawal.
2. Prior to wound punching.
3. Re-check of eligibility criteria.
4. Weight only.
5. Drug tests may also be performed at 1 to 2 additional random occasions during the study.
6. Females only. Screening: blood/serum tests, other visits: urine test.
7. Pre-treatment and 1 and 4 hours (i.e. before the subject leaves the clinic) after dose
8. ECG on Day 10.
9. Prior to first IMP administration. Can be performed at screening or at any time between screening and the first IMP administration.
10. Day 1, cohort 1 only, and Day 19, all cohorts, one sample of resuspended drug product for viable count, see Section 11.6. All cohorts.
11. After wound punching, prior to IMP application and 4 h post application.
12. Local tolerability assessed by the Investigator (direct observation) and by 3 to 5 independent evaluators using photographs. Day 1: after wound punching, prior to IMP application and 4 hours post application. Subjects assess local tolerability from Day 2.

13. Local tolerability during long-term follow-up assessed by the investigator only.

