#### **11.8.3 *Assessment of wound healing and wound rupture***

The Investigator and the independent evaluators will assess the wound healing status of each wound by direct inspection or by evaluation of photographs, respectively, at visits specified in Table 8.1-1 and Table 8.1-2.

Wound healing, i.e. complete wound closure, is defined as skin re-epithelialization without dressing requirements.

The results of the assessment will be reported in the eCRF as “Yes” or “No” per wound. At each post-wound healing visit, it should be documented if the wound is still healed or if any rupture(s) has occurred.

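### MAD part: the independent experts skip the yes/no healing rating on Day 17 although they read that day's photographs for other items, so their healing series jumps from Day 15 to Day 19 (minor)

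*Protocol*

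**What the plan says.** Table 8.1-2 marks wound healing for the Visits 5 to 11 column, for Day 21 and for Day 32. The days in that column are "Day 5, 8, 10, 12, 15, 17, 19 ±1 day on Days 12 to 19". Section 11.8.3 names both sources: "The Investigator and the independent evaluators will assess the wound healing status of each wound by direct inspection or by evaluation of photographs", at the visits given in the schedule. Footnote 20 then makes one exception, for one rater and one day: "No assessment by independent experts on Day 17". No reason is given.

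The other photo readings carry no such exception:
- Local tolerability, footnote 12: "Local tolerability assessed by the Investigator (direct observation) and by 3 to 5 independent evaluators using photographs".
- Wound area, footnote 21: "Wound area assessed by 3 to 5 independent experts using photographs and the Image J software (NIH) or equivalent".
- Scar formation, footnote 23: "by 3 to 5 independent experts using photographs Visit 9 to Visit 12".

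The photographs exist. Section 8.1.2 has the wounds photographed "before treatment on Day 1, pre-treatment at the subsequent dosing visits, and at all follow-up visits to the research clinic", and Day 17 is a dosing visit.

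Section 7.2.1 lists the time course of healing and the frequency of ruptures as secondary endpoints, each with the Investigator and the independent evaluators as named evaluators. Section 17.6.3 plans a yes/no healing result at each visit, frequency tables by treatment, visit and cohort, a correlation with dose, and a non-parametric comparison of active with placebo.

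**The concern.** The photographs are taken and opened by the same readers on that visit, yet the one item that feeds the time course of healing is left out. An expert can enter a scar score and a zero area for a wound on Day 17 and have nowhere to say whether it has healed.

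The experts' closure dates are then coarser than the Investigator's over Days 15 to 19. The two series disagree by construction for some wounds, and the frequency table by visit has an empty expert column for Day 17. The rating is not collected, so no later analysis can recover it. At stake is the precision of one of two sources for a secondary endpoint, and its comparability with the other source.

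**Working it through.** The protocol gives no power, alpha or closure-time figure for this endpoint, so there is no stated number to reproduce. The check is of the schedule, followed by an illustration under assumed closure times.

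**1. Which visit is Day 17.** A footnote to the same table fixes "25. Day 15, Visit 9". Counting through the column gives Visit 5 = Day 5, 6 = Day 8, 7 = Day 10, 8 = Day 12, 9 = Day 15, 10 = Day 17 and 11 = Day 19; Visit 12 is Day 21. The experts' scar readings at Visits 9 to 12 therefore fall on Days 15, 17, 19 and 21 and include Day 17.

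**2. Gaps between healing ratings (days).**

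| Rater | 5–8 | 8–10 | 10–12 | 12–15 | 15–17 | 17–19 | 19–21 | 21–32 |
|---|---|---|---|---|---|---|---|---|
| Investigator | 3 | 2 | 2 | 3 | 2 | 2 | 2 | 11 |
| Experts | 3 | 2 | 2 | 3 | 4 (15–19) | – | 2 | 11 |

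With the ±1 day windows, the experts' interval runs from (19−1)−(15+1) = 2 to (19+1)−(15−1) = 6 days. For comparison, Day 15 to Day 17 runs from (17−1)−(15+1) = 0 to (17+1)−(15−1) = 4 days.

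**3. Effect on the recorded date.** Closure is dated at the first yes.
- Closed after Day 15 and by Day 17: Investigator Day 17, experts Day 19, a difference of 2 days.
- Closed after Day 17 and by Day 19: Day 19 for both.

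For closures spread evenly over Days 15 to 19, the mean delay is half the gap: 4/2 = 2.0 days without the Day 17 rating and 2/2 = 1.0 day with it.

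**4. Dependence on when wounds close.** All closure means, SDs and effects below are assumptions. The first illustration draws normal closure times for one active and one placebo wound and counts pairs recorded on the same day.

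| Mean closure day, active / placebo | SD | Ties with Day 17 | Ties without |
|---|---|---|---|
| 10 / 12 | 2 | 23% | 23% |
| 16 / 18 | 1.5 | 24% | 54% |
| 16 / 18 | 2 | 22% | 42% |
| 16 / 18 | 3 | 18% | 29% |
| 22 / 26 | 3 | 59% | 59% |

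With means of 16 and 18, the recorded medians are Day 17 against Day 19 with the rating and Day 19 against Day 19 without it.

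The second illustration takes a cohort of 8 subjects with 4 active and 2 placebo wounds each, a true advantage of 1.5 days, and a paired t-test on subject means at two-sided 5%.
- Tight spread (SDs: subject 1, arm 0.7, wound 1 day), placebo median closure on Day 17, 18 or 19: power falls from 69% to 56%, 63% to 42% and 52% to 30%. A repeat run agreed to within 1 point.
- Same spread, placebo median on Days 12 to 15 or 22 to 24: loss of about 0 to 2 points.
- Wider spread (subject 2, wound 1.5 days): loss of about 3 to 6 points.
- Widest spread (subject 2, arm 1, wound 2 days): loss of about 0 to 2 points at every median from Day 12 to Day 24.

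**The case against.** **Blinding.** A reader might infer that blinded closure dates as a whole have a hole, or that a rupture seen on Day 17 has no blinded record. The protocol does not support this. Section 9.10 withholds allocation from evaluating clinical staff as well as from the independent evaluators. The Investigator rates healing on Day 17 and, under Section 11.8.3, documents rupture at visits after healing. Nothing in the protocol ranks the photo reading as the better-blinded source.

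**Timing.** A reader might also infer that the gap falls just when closure is expected. The protocol gives no human closure time, and its indirect signs conflict. Expert scar readings start on Day 15 in the MAD part but on Day 14 in the SAD part. The Vancouver score endpoint starts on Day 21. Section 9.6.1 assumes dressing until at least Visit 13 (Day 32), while healing is defined as needing no dressing.

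**Size.** The large power losses need a tight spread, closure near Days 17 to 19 and a t-test that Section 17.6.3 does not plan; Section 17.2 makes no power claim. Nor do active and placebo dates generally collapse together. In the tight setting the mean recorded difference goes from 1.49 to 1.37 days for a placebo median of Day 17 and from 1.71 to 1.28 for Day 18, but rises from 1.31 to 1.80 for Day 15.

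**Other data.** The experts' Day 17 area partly shows closure, although zero area is not the definition of healing. A wound still open on Day 21 is not without a later area either, because the 3D camera is scheduled on Day 32 and measures area, as an exploratory endpoint.

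**The wording of 17.6.3.** Healing is not scheduled on Days 2 and 3, so that section can only mean each visit at which healing is scheduled. Day 17 is such a visit, so the mismatch remains.

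These points limit the size and reach of the issue. None of them supplies a reason for the omission.

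**Conclusion.** The point holds as a minor one. The experts' healing series lacks one of nine scheduled MAD time points, with no stated reason, while the same photographs are read for three other items. The certain consequences are a nominal 4-day interval instead of 2, a built-in 2-day disagreement with the Investigator for wounds closing after Day 15 and by Day 17, and a mismatch with Section 17.6.3.

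The cost in precision is conditional. It can be material if many wounds close around Days 15 to 19 with little spread, and it is near zero if they close clearly earlier or later. The protocol does not say which applies. The omission affects one of two raters on secondary endpoints of a first-in-human study whose primary aim is safety. It is also not the longest interval: Days 21 to 32 span 11 days for both raters, and the repair does not change that.

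**What to change.** Delete the sentence "No assessment by independent experts on Day 17" from footnote 20 of Table 8.1-2, so that the experts record the yes/no healing status on the Day 17 photographs they already read. The Day 15 to 19 interval then splits into 2 + 2 days, and the experts' longest gap before Day 21 falls from 4 to 3 days. The cost is reading time: 24 subjects × 8 wounds = 192 extra yes/no calls per evaluator, or 576 to 960 in total with 3 to 5 evaluators. No photograph, reader or visit is added.

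If the omission is deliberate, state the reason and treat the experts' closure dates as interval-censored between Day 15 and Day 19.

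Optional and also minor: mark expert wound area at Visit 13 (Day 32), using the photograph already taken. After Day 21, area is otherwise available only from the exploratory 3D camera. The cost is one table cell, plus outlines for wounds not yet closed.
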